## Abstract

**Introduction:**

The majority of stage III patients with non-small cell lung cancer (NSCLC) are unsuitable for concurrent chemoradiotherapy, the non-surgical gold standard of care. As the alternative treatment options of sequential chemoradiotherapy and radiotherapy alone are associated with high local failure rates, various intensification strategies have been employed. There is evidence to suggest that altered fractionation using hyperfractionation, acceleration, dose escalation, and individualisation may be of benefit. The MAASTRO group have pioneered the concept of ‘isotoxic’ radiotherapy allowing for individualised dose escalation using hyperfractionated accelerated radiotherapy based on predefined normal tissue constraints. This study aims to evaluate whether delivering isotoxic radiotherapy using intensity modulated radiotherapy (IMRT) is achievable.

**Methods and analysis:**

Isotoxic IMRT is a multicentre feasibility study. From June 2014, a total of 35 patients from 7 UK centres, with a proven histological or cytological diagnosis of inoperable NSCLC, unsuitable for concurrent chemoradiotherapy will be recruited. A minimum of 2 cycles of induction chemotherapy is mandated before starting isotoxic radiotherapy. The dose of radiation will be increased until one or more of the organs at risk tolerance or the maximum dose of 79.2 Gy is reached. The primary end point is feasibility, with accrual rates, local control and overall survival our secondary end points. Patients will be followed up for 5 years.

**Ethics and dissemination:**

The study has received ethical approval (REC reference: 13/NW/0480) from the National Research Ethics Service (NRES) Committee North West—Greater Manchester South. The trial is conducted in accordance with the Declaration of Helsinki and Good Clinical Practice (GCP). The trial results will be published in a peer-reviewed journal and presented internationally.

**Trial registration number:**

NCT01836692; Pre-results.

Strengths and limitations of this study
Radiotherapy delivered using advanced techniques, including intensity modulated radiotherapy (IMRT), 4D-CT and image-guided radiotherapy (IGRT) in all patients.Robust quality assurance (QA) programme.Multicentre study.Single arm study.Heterogeneity of the stage III patient group.

## Introduction

Lung cancer is the leading cause of cancer mortality worldwide^1^ with approximately 40 000 new cases diagnosed annually in the UK. Of these cases 34 000 will present with non-small cell lung cancer (NSCLC) and one-third (∼12 000) of patients with NSCLC will present with locally advanced (stage III) disease. The 5-year survival from lung cancer in the UK has changed little (from 3% to 8%) over the past 60 years, with progress lagging significantly behind other common cancers. The 5-year survival of stage III NSCLC with current standard treatment is approximately 10–15% highlighting a real urgency to improve outcome for these patients.

Radiotherapy (RT), alone or combined with chemotherapy, plays a major therapeutic role in the treatment of stage III NSCLC. Despite this, most patients still progress locally and at sites of distant spread. Concurrent chemoradiotherapy (chemotherapy and RT given at the same time; CTRT) is the standard of care in stage III NSCLC^2^ with median survival rates of approximately 21 months. However, the majority of patients are not suitable for this treatment based on poor performance status (PS) and comorbidities.^3^ In a recent UK national survey of CTRT practice, the majority of clinical oncologists estimated that <30% of patients with stage III NSCLC were suitable for concurrent CTRT.^4^ The alternative treatment offered to patients who are not suitable for concurrent CTRT is sequential CTRT (chemotherapy given prior to RT), but local control and survival rates are inferior compared with concurrent CTRT.^2^ As the majority of patients with stage III NSCLC cannot be treated concurrently, strategies to improve outcome in this large group of patients treated sequentially is vital.

Local control with current RT doses delivered with standard three-dimensional conformal RT (3D-CRT) is poor with local progression-free survival rates of about 30%. However, recent data has shown that improved local control in lung cancer can lead to improvement in survival.^2^ A meta-analysis of concurrent versus sequential CTRT in locally advanced NSCLC based on individual patient data demonstrated that although concurrent treatment decreases locoregional progression (HR=0.77; p=0.01); its effect is not different from that of sequential treatment on distant progression (HR=1.04; p=0.69).^2^ The decrease in locoregional progression translated into a significant survival benefit in favour of concurrent CTRT (HR, 0.84; 95% CI 0.74 to 0.95; p=0.004), with an absolute benefit of 5.7% at 3 years and 4.5% at 5 years.

We are now accelerating into an era of personalised medicine for the systemic treatment of NSCLC. However, to date, fixed doses of radiation are still delivered to patients, not taking into account volume of disease, stage of disease (IIIa vs IIIb) or anatomical location within the thorax. Stage III NSCLC is a heterogeneous disease and there is a need to move away from a ‘one-size-fits-all’ approach to more personalised radiation treatments. The concept of isotoxic RT was recently introduced allowing the radiation dose prescription to the tumour to be tailored based on normal tissue constraints.^5^
^6^

A strategy to improve local control is to escalate the dose of radiation delivered to the tumour. Martel *et al*^7^ demonstrated a clear dose–response relationship in NSCLC, with 84 Gy using conventional fractionation required to achieve 50% probability of tumour control at 3 years. Subsequently we have learnt from the stereotactic body RT studies in NSCLC that biologically effective dose (BED) in excess of 100 Gy are necessary to achieve >90% local control rates.^8^

However, a recent Radiation Therapy Oncology Group (RTOG) phase III study that randomised patients between 60 Gy in 30 daily fractions and 74 Gy in 37 daily fractions has failed to demonstrate a survival advantage for the high-dose arm indicating that dose escalation using a conventional fractionation resulting in increased overall treatment time is not the way forward in this disease. The failure of the high-dose arm was likely multifactorial and in addition to prolonged overall treatment time may have resulted from a combination of poorer treatment delivery with less patients receiving concurrent chemotherapy, reduced compliance to RT, QA issues and unreported treatment toxicity.^9^ Following the presentation of RTOG 0617 a dose of 60 Gy biologically equivalent dose in 2 Gy fractions (EQD2) is considered to be standard in patients with stage III NSCLC.^10^

Accelerated hyperfractionation has been studied in an attempt to reduce the overall treatment time and counteract repopulation in lung cancer. In the national continuous hyperfractionated accelerated radiotherapy (CHART) study there was a staggering 24% reduction in the relative risk of death, which is equivalent to an absolute improvement in 2-year survival of 9% with hyperfractionated accelerated RT (54 Gy in 36 fractions over 12 days) compared with conventional RT (60 Gy in 30 fractions over 6 weeks).^11^ Despite CHART showing this significant benefit, it has not become standard practice in the UK. First, a large percentage of patients included had stage I–II disease (36%) who would now be considered for surgery or stereotactic body radiotherapy (SABR), and second, the control arm would not be considered current standard of care since chemotherapy was not delivered with RT (either sequentially or concurrently). Subsequently an individual patient data meta-analysis of 2000 patients from 10 trials, demonstrated that modified fractionation (acceleration, hyperfractionation or both) improves overall survival as compared with conventional fractionation in NSCLC resulting in an absolute benefit of 3% at 5 years.^12^

Intensity modulated radiotherapy (IMRT) modulates the intensity profile of the radiation delivered to the patient allowing improved targeting of the radiation dose. This technique allows a decrease in the mean lung dose (MLD), V20 (percentage volume of total lung receiving ≥20 Gy), and maximal spinal cord dose. As a result the dose delivered to the tumour can be escalated while keeping the dose to the normal tissue within tolerance.^13^ Although IMRT is becoming standard for the treatment of lung cancer in large international academic centres, in the UK implementation of IMRT is currently poor. In September 2010 Cancer Research UK reported that UK RT practice is ‘lagging behind’ with only 7% of patients receiving IMRT compared with 20% in Europe.

The MAASTRO group have pioneered the concept of ‘isotoxic RT’ allowing for individualised dose escalation using hyperfractionated accelerated RT based on predefined MLD and spinal cord dose in stage I–III patients.^6^ They have shown with 3D-CRT delivered two times a day over 4 weeks that increasing the radiation dose to prespecified normal tissue dose constraints could lead to increased tumour control probability with the same normal tissue complication probability. In the stage III group of patients the mean dose delivered was 61.2 Gy (ie, 72.2 Gy BED10 and 60.2 Gy EQD2), range 50.4–79.2 Gy (ie, 59.5 Gy BED10 and 49.6 Gy EQD2 –93.5 Gy BED10 and 77.9 Gy EQD2) and <10% of patients received the maximum dose as per protocol of 79.2 Gy in 39 fractions two times a day with 3D-CRT (ie, 95.3 Gy BED10, 79.4 Gy EQD2). The survival rates of stage III patients in this study, all of whom were treated with sequential CTRT, were comparable to the results expected with concurrent CTRT with acceptable acute and late toxicity. It is important to note that IMRT was not used in the MAASTRO study. Our in-house planning study, has confirmed the use of IMRT could allow further individual dose escalation in this group of patients, which may ultimately translate into improved survival.^14^

## Methods and analysis

The Isotoxic IMRT study is a non-blinded multicentre feasibility study. The study is sponsored by The Christie NHS Foundation Trust^*^ and coordinated by the Manchester Academic Health Science Centre Trial Co-ordination Unit (MAHSC-CTU) based at The Christie NHS Foundation Trust. Data management is undertaken by the MAHSC-CTU. The trial is registered on the clinicaltrials.gov database (NCT01836692) and jointly funded by Cancer Research UK's Clinical Trials Awards and Advisory Committee (CTAAC) and the British Lung Foundation (BLF). The study is included in the National Institute for Health Research (NIHR) Clinical Research Network portfolio (ID: 14937). The trial is conducted in accordance with the Declaration of Helsinki and Good Clinical Practice (GCP).

The primary research question is to evaluate the feasibility of delivering isotoxic RT using IMRT and hyperfractionated accelerated RT in patients with stage III NSCLC unsuitable for concurrent CTRT.

The secondary research questions are:
Estimate the feasibility of delivering lung isotoxic IMRTEstimate the proportion of patients with acute grade 3+ non-haematological toxicityEstimate late toxicityEstimate local control and overall survivalDevelop a robust QA process for lung IMRT

### Setting

In total, 35 patients with a histological or cytological proven diagnosis of NSCLC will be recruited from seven UK centres: Addenbrookes (Cambridge), Beatson (Glasgow), The Christie NHS Foundation Trust (Manchester), Royal Marsden (London), Northern Ireland Cancer Centre (Belfast), Weston Park (Sheffield), St James's Hospital (Leeds). The study started recruitment in June 2014.

Patients with stage III NSCLC, PS 0–2, not suitable for concurrent CTRT, will be treated with individualised doses of radiation based on prespecified normal tissue doses (spinal cord, brachial plexus, lung tissue, heart and great vessels/proximal bronchial tree table 1). The study flow diagram is shown in figure 1.

**Table 1 BMJOPEN2015010457TB1:** Prespecified normal tissue doses (specified to a volume of 1 cc)

Organ at risk	Prespecified normal tissue doses
Brachial plexus	Maximum dose=EQD2≤66 Gy
Heart	Maximum dose=EQD2≤76 Gy Mean dose ≤46 Gy
Lung	Mean lung dose (lung—GTV) ≤20 Gy
Mediastinal envelope*	Maximum dose=EQD2≤76 Gy
Spinal canal PRV	Maximum dose=EQD2≤50 Gy

*Including: heart, proximal bronchial tree, trachea, oesophagus and the blood vessels in the upper mediastinum.

EQD2, equivalent dose in 2 Gy fractions; GTV, gross tumour volume; PRV, planning organ at risk volume.

**Figure 1 BMJOPEN2015010457F1:**
[figure not shown]
Trial schema. BD, two times a day; CBCT, Cone beam computer tomography; CTRT, chemoradiotherapy; ECOG, Eastern Cooperative Oncology Group; IMRT, intensity modulated radiotherapy; NSCLC, non-small cell lung cancer; PET, positron emission tomography; PTFs, pulmonary function tests; RT, radiotherapy.

### Participant screening and selection

Patients have been deemed inoperable by the lung multidisciplinary team (MDT) and suitable for sequential CTRT. Eligible patients are invited to participate and provided with a patient information sheet (see online supplementary appendix 1). Patients are only registered into the Isotoxic IMRT study once. Mandatory investigations prior to registration included: a Contrasted CT scan of the thorax and upper abdomen (within 4 weeks prior to registration), Contrast-enhanced CT (or MRI) brain scan (within 4 weeks prior to registration if patients have not had imaging of the brain prior to starting induction chemotherapy), fluorodeoxyglucose-positron emission tomography (FDG-PET) CT within 4 weeks prior to registration if patients have not had a PET-CT prior to starting induction chemotherapy and lung function tests.

10.1136/bmjopen-2015-010457.supp1Supplementary appendix 1

### Inclusion criteria

Histologically or cytologically confirmed NSCLCInoperable stage III disease (T3N1-3, any T4, any N2-3) confirmed by PET scanning, mediastinoscopy or thoracoscopyPatients treated with at least two cycles of platinum-based induction chemotherapy and able to start RT within 5 weeks of the last cycle of chemotherapyTumour judged inoperable by a lung MDTAge ≥18, no upper age limitPS—Eastern Cooperative Oncology Group (ECOG) scale 0–2. Patients with PS 2 whose general condition is explained by disease can be included at the discretion of the local investigator. Patients with PS 2 as a result of comorbid conditions will be excludedPatient considered suitable for radical RTTumour that can be encompassed within a radical RT treatment volume (MLD expected to be ≤20 Gy).

### Exclusion criteria

Patients suitable for standard concurrent CTRTPatients only suitable for radical RT alone

### Informed consent

Eligibility to participate is confirmed by a clinician prior to consent being taken. Patients are given at least 24 h to consider the patient information sheet and time to ask questions prior to written informed consent being taken by a trial doctor. The consent form can be viewed in online supplementary appendix 2.

10.1136/bmjopen-2015-010457.supp2Supplementary appendix 2

### Registration

Registration into this study takes place after completion of chemotherapy. Once a patient is deemed eligible for the study and has consented to participate, the MAHSC-CTU will allocate a participant identification number by telephone and confirm enrolment by email.

### Standard care

In patients with inoperable stage III NSCLC who are unsuitable for concurrent CTRT, sequential CTRT is the standard of care. While on study participants will not co-enrol in other clinical trials offering therapeutic intervention. Patients can withdraw from the trial at any time without any effect on clinical care.

### RT intervention and planning

4D-CT scanning is mandatory to account for tumour motion during the breathing cycle. The use of intravenous contrast is mandated (patients with a medical contraindication should not be included in the study). The whole thorax (cricoid to L2) should be covered to allow dose volume histograms to be calculated for the lung, heart, spinal cord, brachial plexus, great vessels, proximal bronchial tree and the oesophagus. RT should be started within 3 weeks of 4D-CT planning scan date.
The motion adapted gross tumour volume (GTV) is defined as identifiable tumour and involved lymph nodes.The clinical target volume (CTV) will encompass regions at risk of microscopic extension.The CTV comprises the GTV with a 5 mm margin of radiologically normal tissue in all directions.CTV to planning target volume (PTV) expansion takes into account patient set-up uncertainties. Tumour motion has been taken into account within the ‘motion-adapted GTV’.The PTV comprises the CTV with a 0.9 cm margin superiorly and inferiorly, and 0.7 cm margin laterally.Editing of the PTV is not permitted.

### Prescribed dose and fractionation

RT doses will be individually escalated until one or more of the organs at risk (OAR) tolerance or the maximum dose of 79.2 Gy is reached. At least 95% of the PTV should receive 90% (ideally 95%) of the prescribed dose and the mean dose to the CTV should be 100%. Hotspots should not exceed 107% of the prescribed dose within a 1 cc volume. IMRT will be delivered two times a day on consecutive weekdays, at 1.8 Gy per fraction, with a minimum 6 h interval between fractions. A maximum of 44 fractions will be delivered for the maximum dose of 79.2 Gy. The overall treatment time should include as few weekends as possible.

Prescribing the treatment using the mean dose to the PTV for lung tumours can be problematic. In certain situations low-density lung tissue at the edge of the PTV can lead to an exaggerated increase in the monitor units needed to achieve the necessary mean dose. For this reason it is suggested that the mean dose will be prescribed to the CTV.

### Dosimetry/dose specifications

Treatment planning will be with inverse planned IMRT. This optimisation must be performed by an experienced dosimetrist/physicist in lung planning.

The use of volumetric modulated arc therapy (VMAT)/RapidArc/tomotherapy/fixed-beam IMRT is allowed in this study. If fixed-beam IMRT is used, it is suggested that five or more fields should be used to avoid creating hot-spots in normal tissue and ensure optimal dose distribution. The use of these techniques facilitate the mandatory PTV coverage of D95 ≥90% (ideally 95%) of the prescribed dose and a 1 cc maximum <107%.

Patients are treated with individualised doses of radiation based on prespecified normal tissue constraints (spinal cord, brachial plexus, lung tissue, heart and great vessels/proximal bronchial tree). RT is delivered two times a day over a maximum period of 4.5 weeks using IMRT and the dose of radiation is increased until one or more of the OAR tolerance or the maximum dose of 79.2 Gy is reached.

### Follow-up

Patients are followed up for 5 years post-treatment (4 monthly in years 1 and 2, 6 monthly from years 2–5). A late toxicity assessment will be performed at each visit.

### Statistical considerations

This feasibility study will be two-stage (with early stopping rules) using the design of Bryant and Day with 85% power and 15% significance level for both completion and acute radiation pneumonitis rates. Using the design of Bryant and Day^15^ to combine an acceptable rate of 90% and unacceptable rate of 70% of patients receiving >60 Gy EQD2 and an acceptable rate of grade 3+ acute radiation pneumonitis of 8.5% and unacceptable rate of 22.5%, 35 patients will be recruited from seven centres over 2 years.

*Stage I*: Enrol 11 patients stop if;
Less than 7 of 11 patients can be planned to a dose >60 Gy EQD2More than 3 of 11 patients experience grade 3+ acute radiation pneumonitis.

If three patients have experienced grade 3+ acute radiation pneumonitis before enrolment of the last patient in stage I, recruitment to stage II would only start when the last patient enrolled in stage I has reached 3 months follow-up. This would be done to ensure the absence of acute radiation pneumonitis in the fourth patient treated before proceeding to stage II.

*Stage II*: Enrol a further 24 patients, totalling 35, conclude a negative study if;
Less than 27 of 35 patients can be planned to a dose >60 Gy EQD2More than 6 of 35 patients experience grade 3+ acute radiation pneumonitis.

There is no planned interim analysis. The study will stop after stage I if the conditions aforementioned are met.

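### The printed two-stage cut-offs give false-positive rates of about 22% (dose) and 29% (pneumonitis), not the stated 15%

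*Protocol article*

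**What the plan says.** All of the design text is in Statistical considerations of the protocol article.

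- **Design:** "This feasibility study will be two-stage (with early stopping rules) using the design of Bryant and Day".
- **Stated properties of that design:** "with 85% power and 15% significance level for both completion and acute radiation pneumonitis rates".
- **Dose endpoint:** "an acceptable rate of 90% and unacceptable rate of 70% of patients receiving >60 Gy EQD2".
- **Safety endpoint:** "an acceptable rate of grade 3+ acute radiation pneumonitis of 8.5% and unacceptable rate of 22.5"%.
- **Stage I (11 patients), stop if:** "Less than 7 of 11 patients can be planned to a dose >60 Gy" EQD2, or more "than 3 of 11 patients experience grade 3+ acute radiation pneumonitis".
- **Stage II (24 further patients, 35 in all), negative if:** "Less than 27 of 35 patients can be planned to a dose >60 Gy" EQD2, or more "than 6 of 35 patients experience grade 3+ acute radiation pneumonitis".

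The section adds a waiting rule. If three stage I patients already have grade 3+ pneumonitis, stage II opens only once the last stage I patient has been followed for three months, so that a fourth case can be ruled out. Trial status reports that recruitment went on to stage II and finished in March 2016.

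**The concern.** The section states both the error rates and the complete rule that is meant to deliver them, so one can be checked against the other without any outside figure. They do not agree.

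This rule is the study's only formal criterion for a negative conclusion. The larger discrepancy is on safety: as printed, a regimen with the pneumonitis rate that the plan calls unacceptable passes nearly twice as often as claimed (28.5 / 15 = 1.9). Under Trial monitoring and oversight, no independent data monitoring committee reviews the data, so a reader of the final verdict relies on these stated properties.

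**Working it through.** **Inputs** (all from Statistical considerations): n1 = 11, n2 = 24, n = 35; dose rate 0.70 (unacceptable) and 0.90 (acceptable); pneumonitis rate 0.225 (unacceptable) and 0.085 (acceptable). As printed, the study continues with at least 7 dose successes and at most 3 pneumonitis events in 11, and is positive with at least 27 successes and at most 6 events in 35.

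**Formulas** (exact binomials)

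- Dose passes: R(p) = Σ over x ≥ 7 of P(Bin(11,p) = x) × P(Bin(24,p) ≥ 27 − x)
- Pneumonitis passes: T(q) = Σ over y ≤ 3 of P(Bin(11,q) = y) × P(Bin(24,q) ≤ 6 − y)
- With independent endpoints: dose error = R(0.70) × T(0.085); pneumonitis error = R(0.90) × T(0.225); power = R(0.90) × T(0.085)

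**Attempt to reproduce 15% / 15% / 85% from the printed rules**

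- R(0.70) = 0.0245 + 0.0588 + 0.0776 + 0.0526 + 0.0143 = 0.228 (x = 7 to 11); R(0.90) = 0.9916
- T(0.225) = 0.0433 + 0.1040 + 0.0967 + 0.0435 = 0.288 (y = 0 to 3); T(0.085) = 0.9675
- Dose error = 0.2278 × 0.9675 = **0.220**
- Pneumonitis error = 0.2876 × 0.9916 = **0.285**
- Power = 0.9916 × 0.9675 = **0.959**

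The stated figures are not reproduced.

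**Does independence matter?** The marginal errors, 0.228 and 0.288, do not use it. Under any association the joint errors cannot fall below 0.2278 + 0.9675 − 1 = 0.195 and 0.2876 + 0.9916 − 1 = 0.279. All of these exceed 0.15.

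**Other readings of the stated figures**

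- Final limits alone, single stage on 35: 23.4% and 29.8%.
- Roles of the two errors reversed: an acceptable regimen is called negative with probability 1 − 0.959 = 0.041. The chance of a negative verdict is then only 1 − 0.220 = 0.780 at the unacceptable dose rate and 1 − 0.285 = 0.715 at the unacceptable pneumonitis rate, both short of 85%.

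**Which cut-offs would meet the stated figures?** Enumerating all cut-offs at 11 and 35 patients leaves nine sets. All nine need at least 28/35 on dose, at most 5/35 on pneumonitis and at most 2/11 on pneumonitis. They differ only in the stage I dose limit, which may be anything up to 8.

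| To continue: dose, pneumonitis (of 11) | To be positive: dose, pneumonitis (of 35) | Dose error | Pneumonitis error | Power |
|---|---|---|---|---|
| ≥7, ≤3 (printed) | ≥27, ≤6 (printed) | 0.220 | 0.285 | 0.959 |
| ≥8, ≤2 | ≥28, ≤5 | 0.108 | 0.144 | 0.861 |
| ≥7, ≤2 | ≥28, ≤5 | 0.117 | 0.146 | 0.872 |
| ≥7, ≤3 | ≥28, ≤5 | 0.121 | 0.162 | 0.904 |

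The second row is the printed numbers 7, 3, 27 and 6 read inclusively (stop at 7 or fewer, or 3 or more; negative at 27 or fewer, or 6 or more). In a search over totals of 30 to 38 patients, it also had the smallest maximum expected sample size (23.8). The stated sample sizes thus fit the stated error rates, while the printed inequalities do not.

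**The case against.** The case against does not dispute the arithmetic. It disputes how far one may go from it, and most of it stands.

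- **A misprint in all four inequalities is not established.** A reader might infer it from the inclusive reading. But the waiting rule makes sense only if three events in stage I allow continuation and a fourth does not, which is the printed limit. A simple slip of sign does not explain that sentence. Nor do all four limits have to move: the stage I dose limit of 7 can stay.
- **Imposing the inclusive reading would create a new contradiction.** With stopping at three events, the waiting rule would have nothing to do.
- **Stage I is over.** Trial status shows that the study passed it and completed accrual, so rewriting the interim limits cannot change what was done.
- **Lenient interim limits are not an error in themselves.** Continuing at 7/11 (64%) or 3/11 (27%), each worse than the corresponding unacceptable rate, may look like one. With 11 patients an interim limit can be that loose while the overall error is still met, as the third row of the table shows for dose.
- **The later randomised trial is not said to depend on this rule.** Trial status places the regimen in a comparison with a standard schedule without tying that step to these cut-offs, and the Primary analysis section is descriptive.

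None of this restores 15%. It limits the diagnosis and the remedy, not the mismatch.

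**Conclusion.** The point holds as a mismatch between stated properties and printed rules. As printed, the design has about 22% error on dose and 29% on pneumonitis with 96% power, against a stated 15%, 15% and 85%. The joint figures assume independent endpoints; the marginal figures and the lower bounds do not, and they lead to the same conclusion.

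The document does not show whether the cut-offs or the error rates were intended. A transcription slip is plausible, but the waiting rule counts against it for the stage I pneumonitis limit. Nor does the mismatch make the study's conclusion wrong. Between the printed final limits and the tighter pair (at least 28, at most 5), the verdict differs only if the final count is exactly 27 on dose or exactly 6 on pneumonitis, with the other endpoint within its printed limit. For other results, the strength of evidence claimed for a positive verdict changes, not the verdict itself.

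**What to change.** 1. Check the four cut-offs, the waiting rule about a fourth patient and the stated error rates against the design calculation, and make the section agree with itself.
2. If the printed cut-offs stand, replace the stated properties with about 22% error on dose, 29% on pneumonitis and 96% power, and interpret the final verdict on that basis.
3. If the check shows that the final limits should have been at least 28/35 and at most 5/35, record this as a late correction made after stage I was passed and recruitment was complete, in a non-blinded single-arm study, with the reason. Report the properties of the rule actually followed: 12.1% and 16.2% error with 90.4% power. The pneumonitis error would still be slightly above 15%, and the report should say so.

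The cost is a wording change and no extra patients. Option 2 leaves the decision rule untouched; option 3 lowers power from 95.9% to 90.4%, still above the stated 85%.

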#### Primary analysis

Total radiation dose, proportion of patients receiving >60 Gy EQD2 to those receiving ≤60 Gy EQD2 and the reason why isotoxic IMRT≤60 Gy EQD2 will be reported.

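### The dose decision rules count patients who can be planned above 60 Gy EQD2, while the hypotheses, power statement, primary analysis and primary question concern the dose received

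*Protocol article*

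**What the plan says.** Four statements in the protocol article concern the dose that patients get:

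- Primary question (Methods and analysis): "The primary research question is to evaluate the feasibility of delivering isotoxic RT using IMRT".
- Power (Statistical considerations): "85% power and 15% significance level for both completion and acute radiation pneumonitis rates".
- Hypotheses (Statistical considerations): "acceptable rate of 90% and unacceptable rate of 70% of patients receiving >60 Gy EQD2".
- Primary analysis: "proportion of patients receiving >60 Gy EQD2 to those receiving ≤60 Gy EQD2", together with total dose and the reasons for not exceeding 60 Gy EQD2.

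The two rules that decide the outcome, also under Statistical considerations, concern the plan. The study stops after stage I if fewer than 7 of 11 patients can be planned above 60 Gy EQD2. After stage II it is negative if "Less than 27 of 35 patients can be planned to a dose >60 Gy" EQD2. Each stage has a parallel rule on acute radiation pneumonitis, which is not at issue here.

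The article nowhere equates planned with received dose. Nor does it say how to count a patient planned above 60 Gy EQD2 who receives less.

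**The concern.** A two-stage design has its stated error rates only if the variable counted by the rule is the variable in the hypotheses. Here they differ. The counts agree for every patient except one who is planned above 60 Gy EQD2 and ends at or below it, by stopping early or never starting. That patient adds to the count needed for a positive conclusion but is a failure under the hypothesis and in the primary analysis.

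The error runs one way, because planned successes can only equal or exceed received successes. The trial could therefore report feasibility by its rule while its own primary analysis shows a received rate at or below the level it calls unacceptable. Delivery is also the open question: the Introduction reports an in-house planning study that already supports dose escalation on paper. The article itself allows for shortfalls, since withdrawal rates are a secondary outcome and the Introduction names reduced radiotherapy compliance among possible reasons why an earlier high-dose arm failed.

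**Working it through.** **Inputs.** From Statistical considerations: stage I n = 11, continue if at least 7; total N = 35, not negative if at least 27; received rate 70% unacceptable, 90% acceptable; pneumonitis rate 8.5% acceptable, 22.5% unacceptable; significance 15%, power 85%. From Prescribed dose and fractionation: 1.8 Gy per fraction, at most 44 fractions. The share q = P(received >60 | planned >60) is an assumption, varied from 1 down to 0.85.

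**1. The plan's own figure.** I took the two endpoints as independent and searched exact Bryant and Day designs for the stated rates, holding both error rates to 15% and power to at least 85%. The best design has 11 patients in stage I and 35 in total, so the sample size reproduces. Its cut-offs are at least 8/11 and 28/35 for dose, and at most 2/11 and 5/35 for pneumonitis. Its error rates are 0.108 (dose) and 0.144 (pneumonitis), with power 0.861. The printed cut-offs are each one patient more lenient, which is a separate issue but sets the baseline below.

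**2. Who is miscounted.** EQD2 = D × (1.8 + 10)/(2 + 10), which agrees with the Introduction (61.2 Gy is 60.2 Gy EQD2).

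- 33 fractions: 59.4 × 11.8/12 = 58.4 Gy EQD2.
- 34 fractions: 61.2 × 11.8/12 = 60.2 Gy EQD2.

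A patient planned to 44 fractions can miss 44 − 34 = 10 and still exceed 60 Gy EQD2. One planned to 34 can miss none. Only patients who end at 33 or fewer after a plan of 34 or more are miscounted.

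**3. A single data set.** Suppose 27 of 35 are planned above 60 Gy EQD2 and three of them fall short. The rule counts 27, which is enough. The received rate is 24/35 = 68.6%, below the unacceptable 70%.

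**4. Operating characteristics.** Hold the true received rate at 70%. The planned rate is then p = 0.70/q, and

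P(dose rule passed) = Σ over x = 7 to 11 of P(Bin(11, p) = x) × P(Bin(24, p) ≥ 27 − x).

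The last column uses the step 1 dose cut-offs, with 8 and 28 in place of 7 and 27.

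| q (assumed) | p = 0.70/q | Printed dose rule (7/11, 27/35) | Rise over q = 1 | Dose rule at 8/11, 28/35 |
|---|---|---|---|---|
| 1.00 | 0.700 | 0.228 | 0 | 0.122 |
| 0.98 | 0.714 | 0.287 | 0.059 | 0.162 |
| 0.95 | 0.737 | 0.394 | 0.166 | 0.242 |
| 0.90 | 0.778 | 0.617 | 0.389 | 0.440 |
| 0.85 | 0.824 | 0.839 | 0.611 | 0.697 |

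If the pneumonitis rule must also be passed, at a true rate of 8.5%, the printed column becomes 0.220, 0.277, 0.382, 0.597 and 0.811.

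**5. Separating two causes.** At q = 1 planned and received coincide, so the excess of 0.228 over 0.15 owes nothing to this mismatch. It comes from the lenient cut-offs. The last column shows the converse: with stricter cut-offs the pass probability still climbs as q falls, so correcting the cut-offs alone would not cure the mismatch.

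**The case against.** The best defence is that isotoxic dose is set at planning, against organ-at-risk limits, so whether a plan above 60 Gy EQD2 can be made is a sensible criterion, especially early. Received dose will be reported under Primary analysis in any case, so a gap would be visible. The article gives no value of q, and near 1 the effect is small. One could also remove the conflict the other way, by restating the hypotheses, power and primary analysis for planned dose.

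Much of this stands. Plan achievability is worth reporting, the size is conditional on q, and restating everything for planned dose would be consistent. But that route would leave the stated primary question, about delivery, without a decision rule. Visibility in the report does not settle which count decides whether the study is negative.

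Three stronger readings are tempting and not supported:

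- *Everyone who does not complete treatment is wrongly counted as a success.* Patients who miss fractions but still exceed 60 Gy EQD2 are successes under the hypothesis too.
- *Patients given no radiotherapy drop out of the primary analysis.* The comparison is clumsily worded, but such a patient received no more than 60 Gy EQD2, and nothing in the text excludes them.
- *The whole distance from 15% is due to this mismatch.* The step to 0.228 is not.

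**Conclusion.** The contradiction is real, lies in the current text, and affects both dose rules. They can return a positive dose conclusion when the received rate is unacceptable, and the stated 15% does not protect against that.

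The size cannot be fixed from the article. At a 70% received rate, the chance of passing the printed dose rule rises from 0.228 to 0.287 if 2% of patients planned above 60 Gy EQD2 fall to or below it, to 0.394 if 5% do, to 0.617 if 10% do and to 0.839 if 15% do. These figures rest on the assumed q and on independent patients with a common success probability; they are a range, not a forecast. If nearly all such patients receive more than 60 Gy EQD2, the practical effect is minor, but the article should still say which count decides.

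**What to change.** Define the dose endpoint once: received a total dose above 60 Gy EQD2. Take all enrolled patients as the denominator (11, then 35), and count as a failure anyone who receives 60 Gy EQD2 or less, including those who never start. Do not add a separate requirement to complete the planned course, which would contradict that definition. Use this endpoint in the decision rules, and report the proportion who can be planned above 60 Gy EQD2 as a supporting figure.

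Trial status gives recruitment as complete in March 2016, so the stage I rule can no longer be changed prospectively. The definition should govern at least the final 35-patient conclusion and be recorded before that conclusion is drawn.

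The cost is small. The sample size stays at 35, and the primary analysis already needs the received dose, so no new data are required. The observed success rate may be slightly lower, and a stage I count of received dose is available later than a planning count. This change does not correct the printed cut-offs: with received dose counted, the dose rule would still be passed with probability 0.228 at a 70% rate, and that needs its own correction.
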